**Methods:**

TENAR is a two-part project, including: 1. a cross-sectional study (involving 250 children and adults with suspected narcolepsy) evaluating the accuracy of Teletriage (i.e., a synchronous live interactive sleep assessment through a Televisit) for narcolepsy diagnosis compared to the reference standard; and 2. a two-arm, parallel, open randomized controlled trial (RCT) to demonstrate the non-inferiority of the multidisciplinary care of narcolepsy through Televisits versus standard care. In this RCT, 202 adolescents (> 14 y.o.) and adults with narcolepsy will be randomly allocated (1:1 ratio) either to Televisits via videoconference or to standard in-person outpatient follow-up visits (control arm). The primary outcome is sleepiness control (according to the Epworth Sleepiness Scale). Secondary outcomes are other symptoms control, compliance with treatment, metabolic control, quality of life, feasibility, patient and family satisfaction with care, safety, and disease-related costs. At baseline and at 12 months, patients will undergo neurologic, metabolic, and psychosocial assessments and we will measure primary and secondary outcomes. Primary outcomes will be also measured at 6 months (remotely or in person, according to the arm).

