**Fig. 1 Fig1:**
[figure not shown]
Flowchart of the randomized controlled trial

**Table 1 Tab1:** Primary and secondary outcomes, measures and timepoints

Outcomes	Measures	Timepoints (months)
Primary		
EDS	ESS (adults) [28] ESS-CHAD [32] (adolescents)	0, 3, 6, 9, 12 incident patients 0, 6, 12 prevalent patients
Secondary		
Other symptoms	Cataplexy diary, NSS [33], BDI [34], STAI [35] (adults) CDI2 [36], MASC [37] (adolescents) Global Impression Scale [38] (physicians)	0, 3, 6, 9, 12 incident patients 0, 6, 12 prevalent patients
Compliance to treatment	Clinical consultation	0, 3, 6, 9, 12 incident patients 0, 6, 12 prevalent patients
Weight	Standard weight scale provided to each patient	0, 3, 6, 9, 12 incident patients 0, 6, 12 prevalent patients
Lipidic/glycaemic control*	Laboratory tests	0, 12
Caloric intake	Food diary	0, 12 [0, 3, 6, 9, 12 patients with metabolic problems]
Physical activity	Short-IPAQ [29]	0, 12 [0, 3, 6, 9, 12 patients with metabolic problems]
Satisfaction index	CoTenar (patients and caregiver)**	6, 12
Quality of life	SF-36 (adults) [39] PedsQL [40] (adolescents)	0, 6, 12
Number (%) of full dropouts		At the time of censorship
Number (%) of partial dropouts (patients changing procedure)		At the time of arm change
Adverse drug reactions	Clinical consultation	0, 3, 6, 9, 12 incident patients 0, 6, 12 prevalent patients
Costs and accidents	Interview (patients and caregivers)	0, 6, 12
Other feasibility indexes	Failure system report (physicians and patients)	After each TV

*Glucose, insulin, HbA1c, triglycerides, total, LDL and HDL cholesterol, TSH, glycaemia, insulin, glycated haemoglobin, HDL, triglycerides, total, LDL, uricemia, TSH, FT4, FT3, complete blood count, AST, ALT, gamma-GT, alkaline phosphatase, creatinine. ** Adapted from CoSM-S [41]

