#### Sample size and statistical considerations

A total of 176 patients (88 per arm) are required to prove that the 95% lower limit of one-sided CI will be above the non-inferiority limit of − 1.5 ESS points difference (standard deviation of 4), with 80% of power. A previous RCT used a non-inferiority margin of 2 ESS points and 80% as minimal power to compare pitolisant versus modafinil in patients with narcolepsy [30]. As the TMC study will not test drugs, we decided to adopt a stricter margin (1.5 ESS points). The standard deviation value (±4) was based on the Italian validation study of ESS [28]. Considering 15% of dropouts, the sample was enlarged to 202 (101 per arm). Repeated measures ANOVA will be used to compare EDS between groups at baseline and after 1-yr of follow-up.

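### The primary ESS comparison is fixed at baseline and 1 year, so the month-6 ESS scheduled for every patient is not used to guard against selective dropout

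*Protocol article*

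**What the plan says.** Under the Tele-multidisciplinary care study, the section Sample size and statistical considerations names both the method and the time points: a repeated measures ANOVA is to be used "to compare EDS between groups at baseline and after 1-yr of follow-up". No other time point enters that sentence.

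The EDS row of Table 1 gives the ESS schedule as "0, 3, 6, 9, 12 incident patients 0, 6, 12 prevalent patients", so month 6 is common to both groups. The abstract confirms it: "Primary outcomes will be also measured at 6 months (remotely or in person, according to the arm".

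Expected losses are met by a larger sample: "Considering 15% of dropouts, the sample was enlarged to 202 (101 per arm". The article describes no other handling of patients without a 12-month ESS.

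**The concern.** With two time points, the group-by-time test of a repeated measures ANOVA is a comparison of mean change between arms. A patient without a 12-month ESS has no change score. If that patient attended at month 6, a primary-outcome value under the allocated care exists but plays no part.

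This matters more than usual here. The trial is open, the claim is non-inferiority, and the margin is narrow. The article itself describes pressures to leave that could differ by arm. Safety assessments and monitoring mentions fear of less accurate assistance and technology barriers with televisits. The Background mentions patients who forgo outpatient visits because of travel cost. If televisit patients whose sleepiness worsened are the ones who leave, the remaining patients make televisits look better than they are, which favours the non-inferiority claim.

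**Working it through.** **1. The plan's own figure.** Inputs from Sample size and statistical considerations: "95% lower limit of one-sided CI" (one-sided alpha 0.05), "we decided to adopt a stricter margin (1.5 ESS points", SD 4 ("The standard deviation value (±4) was based on the Italian validation study of ESS"), power 80%, with a true difference of 0 assumed.

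n per arm = 2(1.645 + 0.842)² × 4² / 1.5² = 2 × 6.185 × 16 / 2.25 = 87.96, so 88 per arm and 176 in total. This reproduces the plan. Then 176 × 1.15 = 202.4, the stated 202. After 15% loss, 202 × 0.85 = 171.7 patients remain (85.85 per arm), with power 79.2% at SD 4.

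**2. Precision from month 6.** The documents give no ESS correlations, so values of 0.5-0.8 are assumed. Write r06, r0,12 and r6,12 for the correlations between months. Let c be the fraction with a month-12 value and m the fraction with a month-6 value. The partial correlation of months 6 and 12 given baseline is

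p = (r6,12 − r06 × r0,12) / √((1 − r06²)(1 − r0,12²)).

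The variance with month 6, relative to the same baseline-adjusted analysis without it, is (1 − p²) + p² × c/m.

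- Low end: all correlations 0.5, and half the dropouts leave before month 6 (c = 0.85, m = 0.925). p = 0.25/0.75 = 0.333; ratio = 0.889 + 0.111 × 0.919 = 0.991; standard error down 0.5%.
- High end: correlations 0.7/0.6/0.8 (0-6, 0-12, 6-12), and all leave after month 6 (m = 1). p = 0.38/√(0.51 × 0.64) = 0.665; ratio = 0.558 + 0.442 × 0.85 = 0.934; standard error down 3.4%.

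This is worth about 2 to 12 patients.

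**3. Selective dropout.** Simulated trials: 101 per arm, SD 4 at each visit, 15% lost, all after month 6, dropout log-odds changing by 1 per SD, and televisits truly 1.5 points worse. Entries are for the completer change score, which is the ANOVA's group-by-time test. Negative bias favours televisits. "Level" scenarios used 6,000 trials each and "worsening" scenarios 4,000.

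| Dropout depends on | Correlations 0-6 / 0-12 / 6-12 | Bias | False non-inferiority |
|---|---|---|---|
| Month-6 level, opposite by arm | 0.5/0.5/0.5 | 0.00 | 5.0% |
| | 0.7/0.5/0.7 | −0.01 | 4.5% |
| | 0.6/0.5/0.7 | −0.10 | 7.0% |
| | 0.3/0.3/0.7 | −0.42 | 14.0% |
| Worsening by month 6, televisit arm only | 0.5/0.5/0.5 | −0.27 | 12.6% |
| | 0.6/0.5/0.7 | −0.36 | 14.4% |
| | 0.7/0.7/0.7 | −0.20 | 11.7% |
| Worsening by month 6, opposite by arm | 0.5/0.5/0.5 | −0.53 | 22.9% |
| | 0.6/0.5/0.7 | −0.72 | 33.4% |
| | 0.7/0.7/0.7 | −0.41 | 22.0% |

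The likelihood analysis with month 6 gave 4.7-5.4% in the six worsening scenarios. Runs over other correlation sets took the change-score rate to about 16% (level, opposite), about 19% (worsening, televisit arm only) and about 45% (worsening, opposite).

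**4. Why the mechanism matters.** The change score shifts with month-6 level by 4 × (r6,12 − r06) points per SD, which is zero when the two correlations are equal. It shifts with month-6 worsening by 4 × (1 + r6,12 − r06 − r0,12) / √(2(1 − r06)) per SD. With all correlations 0.5 that is 2 points. The simulated bias of 0.264 in the companion run with no true difference therefore implies a completer shift of 0.132 SD in one arm. Check at 0.6/0.5/0.7: 4 × 0.6/0.894 = 2.68, and 2.68 × 0.132 = 0.354, against 0.357 simulated. Check for level with opposite selection at 0.3/0.3/0.7: 2 × 0.132 × 4 × 0.4 = 0.42, as in the table.

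**The case against.** The strongest reply is that nothing in the article says patients without a 12-month ESS are excluded. This is a condensed report, and missing-data handling is commonly left to the full protocol or the analysis plan. That stands: deletion is an inference from the named method. It does not dispose of the point, because the article does fix the method and the two time points, and using month 6 would depart from that sentence.

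A reader might go further in four ways that the documents do not support.

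- **That the completer comparison is biased whenever leaving is related to earlier ESS.** It is not: the first two rows of the table show strong, opposite selection on month-6 level with no inflation.
- **That the error rate is 12-29%.** Figures of that size under level-driven dropout belong to a completer ANCOVA, which the plan does not name.
- **That controls alone would skip a final journey.** The abstract ties remote or in-person measurement to month 6. The 12-month assessments and laboratory tests apply to both arms. Questionnaires are completed electronically before each visit, so a missed journey need not mean a missing ESS.
- **That the loss of precision is important.** Section 2 of the working shows that it is not.

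It is also fair to say that months 3 and 9 exist only for incident patients, so a model using them must account for who was scheduled.

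**Conclusion.** The point holds as a worthwhile improvement to a stated analysis choice. It is not an error in any stated figure. The plan collects a month-6 primary-outcome value on every patient and names a primary analysis that does not use it.

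Under the assumptions above, the planned comparison ranges from no inflation to about 14-16% when dropout follows month-6 level with unequal correlations and opposite selection. It is about 12-19% when televisit patients who worsened leave more often, and higher again when worsening drives opposite selection in the two arms. In the tabulated worsening scenarios the bias is 0.20-0.72 points, or 13-48% of the 1.5-point margin (0.20/1.5 and 0.72/1.5). The correlations, the selection strength, the timing of loss and the mechanism are all assumed, so the range shows what could happen and does not predict it.

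**What to change.** Replace the closing ANOVA sentence of Sample size and statistical considerations with a likelihood-based repeated measures model (MMRM) on the scheduled post-baseline ESS values: months 6 and 12 for all, and months 3 and 9 for incident patients. Include baseline ESS and the randomisation stratum (children, adult incident, adult prevalent) as covariates, separate arm-by-visit means and an unstructured covariance. Report the month-12 arm difference with its one-sided 95% limit against the 1.5-point margin. If months 3 and 9 complicate the model, use months 6 and 12 only; that keeps the value common to every patient.

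With free arm-by-visit means, a constant offset between remote and in-person ESS at month 6 does not enter the month-12 contrast.

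The cost is wording and some model specification, with no new visits, data or patients. The downside is reliance on data being missing at random. The model cannot help with patients who leave before month 6, or with dropout driven by unseen month-12 values, so a sensitivity analysis for data missing not at random should go with it.

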#### Safety assessments and monitoring

Patients may face difficulties in accepting TMC for the fear of less accurate assistance or for barriers in the use of mobile technology. We plan to cooperate with AIN for the recruitment and education (e.g., tutorial activities for the tablet use) in order to avoid inappropriate exclusion of patients with technology barriers. The patient, contacting a provider through the tablet, 3-h/week, may request on-call TVs. The same availability will be provided to patients included in the control arm.

With patient consent, the first TVs will be recorded in order to assess the experts’ fidelity to the protocol procedures. Recordings will be destroyed at the end of the assessment. CN will be in charge of monitoring.

#### Data entry, coding, security, and storage

All data will be entered electronically in an ad-hoc design web-based e-CRF. This will be done directly by the patient filling in the forms before each visit (e-questionnaires), or during the visits by the physicians (clinical assessment). The e-CRF is designed and validated for data security and storage according to international standards (US FDA: 21 CFR Part 11; EU GMP: Annex 11; ICH/GCP; VICH/GCP; GAMP 5; GDPR). Personal information about participants will be processed in accordance with the GDPR and national regulation on data protection.

### Ethical approval and informed consent procedures

The study will be conducted in accordance with Helsinki declaration. The Independent Ethics Committee of Area Vasta Emilia Centro (CE-AVEC) approved both the Tele-Triage study and the TMC study (number 18034-120_2018_sper and 18,033-121_2018_sper respectively). Signed informed consent form will be obtained by the sleep experts prior to recruitment. Consent for patients< 18 y.o. will be provided by their parents. Separate assent forms will be signed by minors (aged 12–17 and aged 14–17 for Tele-Triage study and TMC study respectively). Both participants and parents/guardians will be free to withdraw their consent for participation at any time. Participants may request to be informed about results of the study once the study is finished. The results of the TENAR project will be communicated during scientific meetings and AIN’s meetings, and through publication in peer-reviewed journals. We will not involve a professional writer.

## Discussion

Narcolepsy is a rare chronic disease with complex needs encompassing medical and psychosocial aspects. The TENAR project will provide, for the first time, evidence about the feasibility, accuracy, efficacy, and safety of TM procedures applied to the diagnosis and the multidisciplinary care of children and adults with narcolepsy. The project combines a multidisciplinary patient-centered approach to narcolepsy with the possibility of screening and following up patients sparsely living across the country by erasing distance-related barriers. We hypothesize that the Tele-triage and the TMC will guarantee accurate, efficient and safe screening and care of patients with narcolepsy.

First, we expect that the Tele-triage procedure will have a good diagnostic accuracy, namely a high sensitivity in capturing possible patients with narcolepsy. This procedure may ease patient access to highly qualified Sleep centres, reducing the diagnostic gap and its detrimental consequences. This is paramount for people suffering from narcolepsy, especially for the youngest ones. Delayed diagnosis, misdiagnoses, and multiple referrals before receiving a proper diagnosis are frequent in narcolepsy [31] and have negative consequences for untreated patients, their family and the healthcare system. Indeed, the diagnostic gap aggravates the psychosocial and economic burden of the disease [3, 31], while a prompt diagnosis of narcolepsy at a young age seems to reduce the future socio-economic burden of the disease [5].

Second, we expect that the TMC will improve patient-centred outcomes without worsening EDS control. TMC guarantees a face-to-face interaction between patients and physicians working in qualified third level centres care, overcoming the geographical barriers.

If the study results will be in line with our hypotheses, the TENAR study procedures will potentially improve access to a timely diagnosis and care for patients with narcolepsy in Italy and other countries. Given the Directive 2011/24/EU on the application of patients’ rights in cross-border healthcare (http://data.europa.eu/eli/dir/2011/24/oj), and the European Reference Networks for rare diseases (http://www.ern-rnd.eu/), the TENAR project approach may also be a model for the management of other rare disorders, and will offer solutions for remote care of patients residing in areas lacking of specific expertise.

## Data Availability

This manuscript does not contain any data. At the end of the study, datasets and materials will be available from the corresponding Author on reasonable request.

## Abbreviations

BDI: Beck Depression Inventory
CDI2: Children Depression Inventory-2
EDS: Excessive daytime sleepiness
ESS: Epworth Sleepiness Scale
ESS-CHAD: Epworth Sleepiness Scale for Children & Adolescents
ICSD-3: International Classification of Sleep Disorders third edition
MASC: Multidimensional Anxiety Scale for Children
NSS: Narcolepsy Severity Scale
PedsQL: Paediatric Quality of Life Inventory
SF-36: Short Form-36 health survey
Short-IPAQ: Short International Phisycal Activity Questionnaire
STAI: State-Trait Anxiety Inventory
TM: Telemedicine
TV: Televisit
VC: Video consultation
